### Control Group

Participants in the control group will receive (1) standard care, (2) follow-up phone calls from the GRA to remind them to reply to data collection texts, and (3) the opportunity to play MAH at the end of the study. To reduce bias, a scripted interview form will be used, and no “teaching” will occur. Calls will only be to check in with the participants and remind them to collect data. If participants ask questions about managing CINV and other symptoms, the GRA will instruct them to contact their clinic nurse for additional management. In addition, participants will be asked to follow cancer center procedures and call their oncologist if they are having problems or have questions. Contamination between groups is not expected since participants are likely scheduled for chemotherapy at different times and receiving treatment in different areas of the treatment center.

### Outcome Measures

#### Primary Outcome Measures

##### Health Care Resource Use

Health care resource use is defined as any unplanned ED admission or HA and will be recorded via participant report using a dichotomous(Y/N) variable at each follow-up phone contact, text, and treatment visit. Follow-up questions about the reason for the admission, length of time for admission, and treatment will also be asked. The report will be verified by medical record review whenever possible.

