### Aims and Hypotheses

The goal of this project is to examine the effectiveness of the MAH intervention in reducing CINV severity and health care use and increasing functioning and QOL. We aim to:

Aim 1: Examine changes in CINV severity, self-management behaviors, functioning, QOL, cognitive representation, and health care use within the intervention group (IG) from baseline (T_1_) to completion of the study (T_6_).We hypothesize that the IG will report lower levels of CINV severity and health care use and higher levels of self-management, functioning, cognitive change, and QOL from baseline to the completion of the study.Aim 2: Determine efficacy of the MAH intervention by comparing differences in primary outcomes (CINV severity and health care use) and secondary outcomes (self-management behaviors, functioning, and QOL) between the IG and control group at each follow-up visit (T_2_-T_6_) and completion of the study (T_6_).We hypothesize that the IG will report lower levels of CINV severity and health care use at T_2_-T_6_ than the control group.We hypothesize that the IG will report higher levels of self-management behaviors, functioning, and QOL at T_2_-T_6_ than the control group.

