For aim 1, when the outcome of interest in binomial (eg, resource use), a sample of 357 participants, each scheduled to be measured 6 times, achieves a power of 0.90 when using a 2-sided Wald test from a GEE analysis with the binary outcome to test whether a P1(1) of 0.500 differs from a P2(1) of 0.250 at a significance level of .05. P1(0) and P2(0) are assumed to be 0.500. Missing value (MCARs) proportions will be combined to form the pairwise observant probabilities using the independent method. The anticipated proportions missing at each measurement time are 0.00, 0.08, 0.16, 0.24, 0.32, and 0.40. The first row of the autocorrelation matrix of the responses within a participant is assumed to be 1.000, 0.500, 0.250, 0.125, 0.063, and 0.031. Other rows follow the same pattern.

For aim 2, based on the assumption of a nausea severity mean score of 6.20, range from 2 to 9, an SD of 2.44, and a clinically meaningful difference in mean nausea severity score of 1 between the IG and control group, a sample size of 500 participants (250 per group), measured between 6 and up to 30 times (depending on the outcome variable of interest), achieves 87% power to detect a difference between the (fixed) group means. The ratio of the subject-specific slope variance to σ² is 0.100. The correlation between measurements within a participant is 0.100. The test was based on a mixed model regression analysis using a significance level of .05. This power analysis was calculated using PASS 20 (NCSS LLC). Anticipating an attrition rate of ~22%, we will seek to enroll 610 older adults for this study. Attrition to mortality is not expected to be high due to the exclusion criteria for those with less than 6 months to live.

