### Recruitment, Randomization, and Procedures

Successful recruitment and retention strategies previously established by our team will guide this study [27,34,52-54]. A stratified sampling strategy followed by randomization will be used. This sample will mirror Florida demographics and aim to recruit participants in the following percentages: female (51%), male (49%), Black (16%), Hispanic (26.4%), White (77%), and other races (7%). At both clinical sites, a research assistant will screen all new patients for eligibility using their respective electronic medical record systems. Eligible patients will be approached by the research assistant at their first chemotherapy appointment and asked to participate. In our pilot study, this timing acted as a distraction for patients while they waited for chemotherapy to start and did not interfere with treatment, nursing care, or education. In addition, prior to treatment, all patients have received standard written education regarding treatment effects and will expect CINV as a possible effect of treatment; therefore, being approached about the study is not expected to elicit anxiety. Informed consent will be obtained in a private area of the clinic open to the research assistant, and a copy of the consent form will be given to the participant.

Once informed consent is obtained, baseline measures will be completed, and participants will be randomized (IG and ACG) to either group by choosing an envelope with a group assignment. If they are randomized to the IG, the intervention will begin immediately. Regardless, participants in each group will receive standard care (1) on admission to the cancer center (receipt of standard written educational materials that patients are instructed to bring to each appointment), (2) at a treatment planning visit in the clinic (receipt of specific handouts regarding treatment and potential side effects, and (3) at time of treatment (verbal review of chemotherapy and symptom handouts by treatment center or chemotherapy nurses). Retention of all participants will be enhanced with (1) weekly follow-up telephone calls and (2) ACG offered MAH at the end of the study.

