#### Part 3: Follow-Up

Participants will be allowed to play the game as many times as they choose during that chemotherapy visit or at subsequent visits in order to practice making decisions and visualizing consequences and outcomes. Once the participant is discharged home, the graduate research assistant (GRA), blinded to the treatment group, will call participants weekly to see how they are doing and remind them to respond to data collection texts or use paper or pencil forms. To reduce bias, a scripted interview form will be used, and no “teaching” will occur. Calls will only be to check in with the participants and remind them to collect data. If participants ask questions about managing CINV and other symptoms, the GRA will instruct them to contact their oncology team for additional management. In addition, participants will be asked to follow cancer center procedures and call their oncologist if they are having problems or have questions.

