##### Experiential Characteristics

Experiential characteristics include cancer diagnosis and stage, chemotherapy regimen with antiemetics, additional treatments (eg, radiation therapy), discharge antiemetic prescriptions, fluids during treatment, changes to the treatment plan (ie, delays in treatment, chemotherapy dose reductions, and changes in chemotherapy), and number of times game is played. All cancer information will be collected from the patient’s electronic medical record by the research assistant.

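### Unplanned ED visits and admissions, a primary outcome, rest on reports from participants who know their arm, and the plan states no route to events that go unreported

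*Protocol article*

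**What the plan says.** The Aims and Hypotheses section sets up the between-arm comparison as "comparing differences in primary outcomes (CINV severity and health care use"), so health care use is one of two primary outcomes.

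Under Health Care Resource Use, an unplanned ED or hospital admission "will be recorded via participant report using a dichotomous(Y/N) variable at each follow-up phone contact, text, and treatment visit". Follow-up questions ask about the reason, duration and treatment. Then comes the only sentence on records: "The report will be verified by medical record review whenever possible".

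On who knows the arm, participants pick an envelope, and "If they are randomized to the IG, the intervention will begin immediately" (Recruitment, Randomization, and Procedures). Controls get "the opportunity to play MAH at the end of the study" (Control Group). The only role described as blinded is the weekly caller: "the graduate research assistant (GRA), blinded to the treatment group, will call participants weekly" (Part 3: Follow-Up).

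On routine record use, Experiential Characteristics has cancer information taken from the "electronic medical record by the research assistant". The items listed there are diagnosis, regimen, antiemetics, fluids and changes to the treatment plan. ED visits and admissions are not among them.

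**The concern.** Checking a report against a record can remove a false or misclassified event. It cannot add one that nobody mentioned. The rule therefore corrects errors in one direction only.

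This matters because the person supplying the outcome knows the allocation. The Discussion gives avoidance of unplanned ED visits and admissions as a purpose of the game, so intervention participants may know which answer is hoped for. Research assistants deliver the game and also meet participants at the later treatment visits, one of the three reporting channels.

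Non-response is a second route to loss. A participant in hospital may miss texts or a treatment visit, so a missing report may be related to the event itself. The site record could supply some of those events, but the rule does not call for it.

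If reporting completeness differs by arm, the comparison shows a difference that is not one of health care use, or hides one that is. A larger sample does not remove this bias.

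**Working it through.** **1. The plan's own figure.** The power section gives 357 participants for the binary outcome. Inputs: proportions 0.50 to 0.50 in one group and 0.50 to 0.25 in the other; six measurements; autoregressive correlation with ρ = 0.5; missing proportions rising from 0 to 0.40; two-sided α = 0.05; power 0.90. For a test of two logit slopes on equally spaced times from 0 to 1, with equal groups:

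N = (1.960 + 1.282)² × V / (β₁ − β₂)²

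Here β₁ = 0, β₂ = ln(0.25/0.75) = −1.0986, and V is the sum over groups of the robust slope variances, scaled for 1:1 allocation. The result is 356.03, rounded up to 357. The stated sample size reproduces and is not at issue. The calculation has no term for incomplete reporting.

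**2. Inputs for the illustration.**
- From the document: 250 per arm (aim 2 power text). Background rates of about 20% for ED visits and up to 47% for CINV-related admission (Introduction). Proportions of 0.25 and 0.50 (power text). These serve only to span a range of true event rates p.
- Assumed: reporting sensitivity of 90% in control and 80% in intervention. The documents give no sensitivity for either arm.
- No true effect: p is the same in both arms.

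**3. Formula.** Observed rates are p_C = 0.90p and p_I = 0.80p, with difference d = p_C − p_I and mean p̄.

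SE₀ = √[2p̄(1 − p̄)/250]

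SE₁ = √[p_C(1 − p_C)/250 + p_I(1 − p_I)/250]

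P(significant) = Φ[(d − 1.960·SE₀)/SE₁] + Φ[(−d − 1.960·SE₀)/SE₁]

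**4. Worked case, p = 0.20.** p_C = 0.18, p_I = 0.16, d = 0.02, p̄ = 0.17. SE₀ = 0.03360 and SE₁ = 0.03359. The two terms are Φ(−1.365) = 0.086 and Φ(−2.556) = 0.005. The sum is 0.091.

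**5. Results.**

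| True rate, both arms | Observed, control vs intervention | Observed risk ratio | P(significant), 90% vs 80% | P(significant), equal reporting |
|---|---|---|---|---|
| 20% | 18.0% vs 16.0% | 0.89 | 9% | 5% |
| 25% | 22.5% vs 20.0% | 0.89 | 10% | 5% |
| 47% | 42.3% vs 37.6% | 0.89 | 19% | 5% |
| 50% | 45.0% vs 40.0% | 0.89 | 20% | 5% |

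The risk ratio is 0.80/0.90 = 0.89 whatever the event rate. The test is two-sided, so swapping the sensitivities gives the same probabilities with the spurious effect reversed.

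**The case against.** The strongest case for the plan has four parts.

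**The text sets no trigger.** The report is a yes/no entry, so a no is also a report and could be verified. A reader might infer from the rule that unreported events are never found, and the document does not support that. What stands is narrower: it does not say that no-answers are checked, and even that reading leaves out participants who give no answer.

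**Contacts are frequent and partly blinded.** Texts go out daily in the first week of a cycle and then every third day, with weekly calls and treatment visits as well. An event missed once may be reported later. The caller is blinded and uses a script in both arms. This limits recall loss and interviewer influence, but it does not blind the participant.

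**The size and direction are not known.** A reader might assume a wider gap, such as 90% versus 75%, and quote false-positive rates of 18% (true rate 25%) to 40% (true rate 50%). The arithmetic is right, but the gap has no source in the documents. Nor does being taught to manage nausea at home imply concealing an admission. The calculation is also a single test of proportions, whereas the plan uses a covariate-adjusted mixed model over repeated visits.

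**Missing data.** The power section states that "The anticipated proportions missing at each measurement time are 0.00, 0.08, 0.16, 0.24, 0.32, and 0.40". A reader might take this to mean that 40% of the between-arm primary outcome will be missing by T6. It is an input to the aim 1 power calculation, assumed completely at random and tied to scheduled measurements. The aim 2 text gives about 22% attrition. Some loss may also be planned end of follow-up, because the End Points section ends participation when chemotherapy stops or is unreasonably delayed.

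An article may leave the mechanics of chart review to a fuller document. Which source defines the primary outcome is not such a detail. The article states it, and states it as report first, record second.

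**Conclusion.** The point holds as a weakness in a stated ascertainment rule. A primary outcome depends on report by participants who know their arm, record review is described only as verification of that report, and no route is given to events that are unreported or fall in a period of non-response. Reporting could therefore differ by arm.

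Under the assumed ten-point gap in sensitivity, the false-positive rate would be about 9% to 20% for true rates of 20% to 50%, against 5% with equal reporting. This shows how sensitive the comparison is. It does not forecast bias in this trial. It rests on the assumed sensitivities, no true effect, 250 analysed per arm and one unadjusted test. The change is worth making because it is cheap.

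**What to change.** Amend the Health Care Resource Use section as follows.

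- Review the site electronic record for unplanned ED visits and hospital admissions in every randomised participant, from randomisation to that participant's own end of follow-up under the End Points section, regardless of what was reported or whether they responded.
- Use one checklist in both arms. Have existing staff abstract without sight of the arm where feasible, since research assistants deliver the intervention.
- Count an event if it appears in the record or in a self-report.
- Add a sensitivity analysis restricted to record-confirmed events.

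**Cost.** Chart-review time. One batched review per participant is 500 to 610 reviews. Separate reviews for each of five intervals would be 2,500 (500 × 5) to 3,050 (610 × 5), so batching is preferable. Staff already open these records for eligibility screening and treatment data, and the review can cover participants already enrolled.

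**Limit.** Events at outside hospitals would still rely on self-report, and the documents do not say what share of events that is.

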##### CINV Severity

CINV severity will be collected on the web using texted links to surveys and will include the presence and severity of CINV (0-10 Likert scale). Participants without a smartphone will be provided the paper and pencil Symptom Management Checklist (SMC; see Data Collection section) to record this data.

#### Secondary Outcome Measures

##### Self-Management Behaviors

CINV prevention and self-management actions, effectiveness of actions (0-10 Likert scale), and amount of hydration will be recorded using the SMC that was used in the pilot study to measure CINV severity and prevention and self-management behaviors. Participants will be asked to record their highest level of nausea each day and preventative self-management actions for CINV and hydration. When experiencing CINV, the participant will use the SMC to record (1) CINV severity (0-10 Likert scale) prior to self-management, (2) the type of self-management strategies used, and (3) the strategies perceived helpfulness in reducing nausea (0-10 Likert scale). All self-management strategies are coded (eg, “MED”=taking antiemetic and “DIS”=using distraction), and the participants will fill in the strategy code they are using on the form. Participants with a smartphone will complete this form electronically, and those without a smartphone will use the paper or pen version, which will be collected by the research assistant at each chemotherapy cycle visit.

##### Symptom Severity

Part I of the Symptom Representation Questionnaire [55] has a 24-item self-report measure that will be used to identify the presence and severity of common treatment-related symptoms (0- to 10-point Likert scale), including nausea and vomiting. This measure asks respondents to think about their symptoms over the past week.

##### Cognitive Representation

Part II of the Symptom Representation Questionnaire [55] has an additional 15 questions to assess cognitive representation (identity, cause, timeline, consequences, and cure or control) or beliefs about specific symptoms (0-4 agreement scale). This measure includes subscales for symptom cause (2 questions), timeline (3 questions), cure or control (3 questions), and consequence (6 questions). Only the cognitive representation of nausea will be evaluated. Original reliability statistics for this instrument were fair (Cronbach α=0.63-0.88 for the subscales) [55], and our pilot showed a Cronbach α of 0.64. The cognitive representation questions will be modified at baseline to assess participants’ beliefs about potential CINV consequences and their ability to be controlled or cured. These data will be collected again at the end of the study.

##### Health-Related QOL

The European Organization for Research and Treatment of Cancer-30 [56] will measure QOL at each treatment cycle. This frequency is consistent with other studies that have measured QOL in older adults over time [57,58]. This well-known scale includes 5 functional scales, 3 symptom scales, and 6 single items using a 4-point Likert scale (1=not at all to 4=very much), and 2 global health or QOL items using a 7-point Likert scale (1=very poor to 7=excellent). Higher scores on the functional and health or QOL scale indicate better functioning, while higher scores on the symptom-related scales and items indicate higher symptoms. The tool was previously shown to be reliable in studies with older adults (Cronbach α=0.89) [56] and had a Cronbach α of 0.80 in our pilot study.

#### Additional Measures

##### Sociodemographic Characteristics

Sociodemographic characteristics include age, gender, race or ethnicity, comorbidity information, education level, and income level. These characteristics will be measured at T_1_ (baseline).

##### Experiential Characteristics

Experiential characteristics include cancer diagnosis and stage, chemotherapy regimen with antiemetics, additional treatments (eg, radiation therapy), discharge antiemetic prescriptions, fluids during treatment, changes to the treatment plan (ie, delays in treatment, chemotherapy dose reductions, and changes in chemotherapy), and number of times game is played. All cancer information will be collected from the patient’s electronic medical record by the research assistant.

### Data Collection

Once enrolled in the study (T_1_—baseline), research assistants will electronically record information about the participants’ diagnosis and treatment plan collected from medical records. Participants in both groups will complete baseline questionnaires electronically on an iPad given to them by the research assistant. The research assistant will demonstrate how to complete the electronic questionnaire and assist with any questions or issues that may occur during data collection. The research assistant will also meet with participants at subsequent treatment cycles (T_2_-T_6_) to have them fill out the electronic questionnaires on the iPad. Assistance will be given as needed.

Between treatment cycles, we will collect information about CINV severity, self-management behaviors, and any ED visit or HA from all participants. Participants with smartphones will be asked to respond to SMS text messages that will provide a link to the SMC, where they will electronically record information about their CINV severity, self-management behaviors, and any ED visit or HA. Participants will receive SMS text messages daily for the first week after treatment and then every 3 days until their next cycle of chemotherapy. This pattern will repeat at each treatment cycle. Current research supports the use of SMS text messaging since it is estimated that ~77% of older adults use smartphones. In total, 81% of adults ages 60 to 69 years report use of smartphones [49], and 79% of those ages 70-74 years report use of smartphones [59]. Research assistants will provide a tutorial on how to use the electronic links and enter data prior to the end of the first appointment. Participants without smartphones will be given a paper and pencil version of the SMC. They will be asked to record data on their daily CINV severity, self-management behaviors, and any ED visit or HA. The paper and pencil method of data collection was successfully used in the pilot study with ~75% of participants at least tracking fluids and ~64% tracking self-management behaviors over time [34]. All participants will be contacted weekly by a GRA, blinded to their treatment group, to assess how they are doing, answer any study-related questions, and encourage participants to reply to the texts or complete the paper and pencil data collection. The GRA will not manage the care of participants while they are in the study, instead, they will refer participants to their oncology team if they have questions or concerns about treatment-related side effects they are experiencing.

### Data Management and Integrity

All data will be stored using REDCap (Research Electronic Data Capture; Vanderbilt University) [60], a secure web application database, which will be accessed by a secure web connection with authentication and data logging. Due to the multisite feature of this study, 2 separate REDCap systems will be set up on the University of Miami and University of Central Florida servers separately, but they will share the same structure so that the data could be communicated and analyzed in a consistent way. For surveys that will be filled out by participants electronically, a secured and unique link will be sent via email or text so that the data can be captured accurately. A unique identifier associated with each participant will also be incorporated into the surveys so that the survey responses could be easily identified and rechecked by research staff. Research assistants will also use this identifier when they enter data from the electronic medical record and from their checklists. For any paper and pen surveys, the project director or research assistants will review all data for completeness and appropriate entries before it is entered into the study database.

At the beginning of the data entry process, a minimum of 1 in every 10 participant records will be checked against the original record for data errors. Records for review will be randomly chosen by the data manager. As the study progresses, the frequency of monitoring will be based on the results of the previous data review. If the error rate is unacceptable, then the monitoring will increase until the error rate is acceptable (less than 5% of all data). In consultation with the principal investigator (VL), the data manager will develop reports that will help in the coordination and management of the project and also allow project staff to monitor the quality of the data and the progress of the study. The data files will be backed up daily during the data entry process and once a month when data collection is complete by the data manager. All data files will be housed on the university servers, which are backed up every 24 hours, and copies will be stored off-site for additional security. Access to the database will be password-protected and limited to the investigators, research personnel, project director, and data manager. Furthermore, the user rights will be assigned appropriately by the project manager or data manager to ensure data security and privacy.

